## Abstract

**Introduction:**

Primary biliary cholangitis (PBC) is a rare chronic cholestatic disease that despite current therapy has significant ongoing unmet needs, including risks of cirrhosis and life-impairing symptoms. The current treatment approach is a step-up model, wherein first-line therapy, ursodeoxycholic acid (UDCA), is given for a minimum of 12 months before the addition of second-line therapy is considered for non-responding patients. This ‘waiting to fail’ approach, focused on the needs of low-risk patients, allows, we postulate, a key process of biliary epithelial cell (BEC) senescence to become established, driving accelerated bile duct loss and aggressive disease. Preclinical mouse modelling has shown that early use of the farnesoid X receptor agonist obeticholic acid (OCA), currently only used as second-line therapy following UDCA failure, reverses BEC senescence, changing the clinical course of disease. Here, we describe the design of the Optimising Primary thErapy in pRimAry biliary cholangitis (OPERA) trial. The aim of OPERA is to explore a new paradigm for disease-modifying treatment of PBC: risk-informed early treatment stratification, with patients at increased risk offered UDCA and OCA combination with the goal of complete biochemical remission.

**Methods and analysis:**

OPERA is a multicentre, randomised, double-blind, placebo-controlled trial of OCA in combination with UDCA, as first-line treatment for high-risk PBC. This is a multicentre trial in England, which will be undertaken in specialist clinics in secondary/tertiary referral centres (or as per local set up). These centres will be specialists in the area of PBC management and will manage patients from across their local region. OPERA will recruit and randomise 106 adults, within 6 months of PBC diagnosis, who are at an enhanced risk of non-response to standard first-line therapy, between either: (1) UDCA and OCA or (2) UDCA and matched placebo in a 1:1 ratio. The primary efficacy outcome measure is the percentage of participants showing normalisation of serum alkaline phosphatase and total bilirubin values at 26 weeks (disease remission).

**Ethics and dissemination:**

Favourable ethical opinion was received from London – Riverside Research Ethics Committee (reference: 22/LO/0878). Potential participants will be fully informed of their rights and the benefits and harms of the trial by the research team before giving informed consent to participate in the trial. Results will be disseminated in peer-reviewed publications, at national and international conferences, in peer-reviewed journals and to participants and the public (using lay language).

**Trial registration number:**

ISRCTN17176388.

STRENGTHS AND LIMITATIONS OF THIS STUDYThis protocol presents a randomised controlled trial designed to evaluate the effect of obeticholic acid (OCA) as a first-line therapy for primary biliary cholangitis patients, challenging the potentially flawed ‘step up’ therapy model that potentially leaves the highest risk patients untreated for a significant period of time, assessing the impact of a more contemporary top-down, disease modification approach.The trial uses biochemical remission (normalisation in serum alkaline phosphatase values) as the efficacy outcome measure, as opposed to the conventional, but flawed, biochemical response indices, which tolerate ongoing disease activity.A biopsy sub-study will allow, for the first time, the mechanism of OCA on bile duct injury and, in particular, the role played by cellular senescence to be addressed.The trial uses a novel statistical method to reduce the sample size required without sacrificing statistical power.The trial relies on a biochemical surrogate marker of outcome, as it is not designed or powered to explore true clinical outcomes; additionally, it only explores one of the potential therapies applicable in this setting.

## Introduction

 Primary biliary cholangitis (PBC) is a rare chronic cholestatic liver disease with significant unmet needs despite current therapy. PBC prevalence is 40/100 000 in the UK with an estimated incidence of 1–2/100 000 per year.^1^ Clinical impact in PBC comes from the risk of progression to cirrhosis with its associated complications and, alongside, difficult-to-treat symptoms; specifically pruritus, fatigue and cognitive dysfunction, that can occur at any point in the disease course, and which result in significant impact on health utility.^2^,^9^ Current standard care is a step-up model, wherein first-line ursodeoxycholic acid (UDCA) is given for a minimum of 12 months before more effective ‘add-on’ therapy is considered for non-responding or under-responding patients.

At a population level, UDCA improves serum liver biochemical markers, delays liver transplantation and increases life expectancy.^210^,^13^ However, approximately 40% of UDCA-treated patients still go on to develop cirrhosis (40% in a multicentre study of >1000 patients over 10 years^14^; 46% of patients in contemporary USA ‘real world data’ report of 15 875 patients,^15^ 60% display persistently abnormal liver blood tests despite UDCA (59% in a UK-PBC nested cohort of 400 patients)^16^ and >80% continue to experience symptoms, especially fatigue and cognitive symptoms that are seemingly not modified by any current intervention.^2 3 9 17^

Current treatment paradigms grant access to the licensed second-line therapy obeticholic acid (OCA; a first in class farnesoid X receptor agonist) given in addition to UDCA, only after patients are deemed to be ‘non-responders’ to UDCA. This ‘step-up’ approach means that the most effective agent is only used after first-line therapy has been tested (and failed) for at least a year.

In PBC, UDCA treatment failure does not occur at random; studies from UK-PBC have clearly shown that UDCA treatment failure can be accurately predicted by pretreatment clinical parameters including the patient’s age and serum biochemistry.^10^ These parameters can be used to produce an accurate predictive UDCA Response Score (URS) that has been validated in Italian and Japanese as well as UK populations.^18^

The impact of waiting to institute more effective therapy in UDCA non-responders goes beyond delaying deriving clinical benefit. The lost time may actually change the trajectory of the disease by allowing key disease processes to become embedded. Critically, UK-PBC studies have demonstrated that therapy delay in PBC leads to a significantly reduced likelihood that the therapy will work when eventually used.^10^ The importance of biliary epithelial cell (BEC) senescence in disease pathogenesis, its contribution to the high-risk phenotype (including progression to irreversible bile duct loss), and the fact that it begins early in the disease process in high-risk patients (and is progressive thereafter) affords a potential explanation as to why treatment delay results in reduced effectiveness. This emphasises the need for earlier, better and more efficient treatment models—a concept that underpins the Optimising Primary thErapy in pRimAry (OPERA) trial concept.

In the OPERA trial, we will evaluate a novel treatment strategy in newly presenting PBC patients; we will use the validated URS to identify, at the point of disease diagnosis, patients who are at reduced likelihood of achieving biochemical remission in response to UDCA monotherapy, and will implement a risk-determined stratified approach whereby the licensed second-line therapy (OCA) is used from the outset in combination with existing first-line therapy.^10^ This strategy will allow us to optimise treatment delivery in the higher risk group early on, without over-treating the lower risk patients. We will also adopt an emerging, evidence-based primary outcome of complete disease control (normalisation of liver biochemistry).

This trial will adopt a dosing regimen optimal for reaching effective doses of OCA, while avoiding pruritus in a trial design setting where liver function test levels are not appropriate for use in assessing efficacy and guiding dose escalation.

As noted in, Clinical effectiveness of Obeticholic Acid (section 4.4) of the NICE guideline for OCA in PBC^19^ and based on the findings of the POISE Trial,^20^ clinical effectiveness of OCA would be better measured at 10 mg. The OPERA trial will close this gap in the literature by measuring an observable disease modifying effect within the trial time frame of 26 weeks. 26 weeks is long enough to observe a disease modifying effect and short enough to allow discontinuation of therapy.^21 22^ If a relapse is experienced by the participant after 26 weeks, they will be assessed for suitability to introduce OCA at 1 year post-UDCA start, according to current National Health Service (NHS) standard of care.^23^

In parallel, we will validate and explore the clinical utility of a mechanistic composite biomarker linked to BEC senescence, based around circulating levels of the chemokines CCL20 and CXCL11.^24^ These parameters will be used to predict and quantify the response to second-line therapy instituted early, comparing it to clinical outcomes, and to the gold standard of liver biopsy assessment of BEC senescence. This marker, developed in UK-PBC pilot studies, has a positive predictive value of 94%, a negative predictive value of 78%, and an area under the receiver operator curve of 0.91 for the identification of UDCA non-responding patients stratified using the current clinical criteria.^24^

## Methods and analysis

### Trial design and setting

OPERA is a double-blinded, superiority, randomised, placebo-controlled, multi-centre clinical trial of an investigational medicinal product (CTIMP). This is a multicentre trial in England, which will be undertaken in specialist clinics in secondary/tertiary referral centres (or as per local set up). These centres will be specialists in the area of PBC management and will manage patients from across their local region. To improve trial efficiency, we will also use an innovative augmented binary analysis method^25^ to improve the precision of a trial where a dichotomous endpoint is derived from continuous data. Using this method substantially reduces the sample size needed for a power of 90%.

The trial population will be newly diagnosed, non-cirrhotic PBC patients, with less than 3 months treatment with UDCA at the time of consent and at an enhanced risk of not achieving biochemical disease remission (based on URS) with UDCA first-line therapy alone. Potentially eligible participants will be invited for a screening visit where informed consent will be received (online supplemental material). Patients will be encouraged to ask questions and will be informed of their right to withdraw from the trial. Potential participants will have sufficient time to review the trial documentation prior to this screening visit. Consent for the optional biopsy sub-study will be through an optional clause on the main trial informed consent form. The trial comprises a 26-week treatment phase in a cohort of 106 participants (OCA n=53; placebo n=53), followed by a 26-week follow-up period. All participants will continue to receive standard of care background treatment with UDCA throughout the trial.

### Objectives and outcomes

The primary and secondary objectives for the trial are described in table 1.

**Table 1 T1:** Objectives and outcome measures

Objectives	Outcome measures
Primary	
To assess the impact of first-line obeticholic acid therapy combined with UDCA, compared with placebo combined with UDCA, in achieving biochemical remission of disease in new onset PBC patients with an enhanced disease risk.	Percentage of participants showing normalisation of serum alkaline phosphatase and total bilirubin levels at 26 weeks (visit 5)—defined as biochemical remission.
Secondary	
(a) To assess whether biochemical remission is sustained following discontinuation of experimental therapy and reversion to UDCA standard of care therapy.	(a) Percentage of participants in each arm showing sustained normalisation of serum alkaline phosphatase and total bilirubin levels at 52 weeks (visit 6).
(b) To assess the degree of biochemical improvement with obeticholic acid therapy combined with UDCA standard of care therapy compared with placebo.	(b) Magnitude of alkaline phosphatase and bilirubin reduction from baseline to 26 weeks (visit 5), assessed as a continuous variable.
(c) To assess impact of obeticholic acid therapy combined with UDCA standard of care therapy compared with placebo using conventional therapy response criteria (as used in current clinical practice).	(c) Percentage of participants attaining serum alkaline phosphatase values lower than 1.67× the upper limit of normal and a bilirubin <1× the upper limit of normal at 26 weeks (visit 5). These are termed the POISE criteria and are widely applied as outcome measures in conventional clinical trials of second-line PBC therapy. Change in liver stiffness assessed by Transient Elastography (FibroScan) from screening to week 26.
(d) To assess the safety and tolerability of obeticholic acid as first line therapy in PBC.	(d) AE and SAE Reporting up to 26 weeks (visit 5).
(e) To assess the impact of the intervention compared with placebo on symptom severity and participant quality of life.	(e) PBC-40 (change from baseline to 26 weeks (visit 5) and 52 weeks (visit 6)). (f) EQ-5D-5L (change from baseline to 26 weeks (visit 5) and 52 weeks (visit 6)). (g) Patient Health Questionnaire (26 and 52 weeks).
Experimental	
(a) To assess whether biochemical remission is sustained following discontinuation of experimental therapy and reversion to UDCA standard of care therapy in those participants who are in remission at 26 weeks.	(a) Percentage of participants in each trial group who remain in remission at 52 weeks (visit 6) as a proportion of those who showed normalisation of serum alkaline phosphatase and total bilirubin levels at primary end-point assessment at 26 weeks (visit 5).
(b) To assess changes in chemokine levels in the blood potentially associated with bile duct senescence.	(b) Serum levels of putative senescence-associated chemokines, demonstrated to be elevated in high-risk disease and UDCA non-responders in underpinning UK-PBC studies as outlined earlier, will be quantified using a bespoke multiplex assay and evaluated as dynamic risk and response markers. The combination of CCL20 and CXCL11 will be specifically explored as a baseline and early response predictive biomarker and validated against liver biopsy findings. Assessment of the capacity for ongoing elevation of chemokine biomarkers at 26 weeks to predict biochemical relapse at 52 weeks.
(c) To assess impact of intervention compared with placebo on degree of liver inflammation and bile duct senescence.	(c) Change in liver fibrosis stage on liver histology and the degree of bile duct senescence assessed using p16 and p21 immunohistochemistry in a biopsy sub-study (n approx. 15 in each group). p16 and p21 are established and well-validated cellular markers of senescence ^25^. Biopsies will be centrally read by two pathologists blinded to treatment allocation and findings correlated with serum chemokine marker values.

AE, adverse event; EQ5D5L, EuroQol - 5 Dimensions - 5 Levels; PBC, primary biliary cholangitis; POISE, Predicted Risk of End-Stage Liver Disease; SAE, serious AE; UDCA, ursodeoxycholic acid.

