### Eligibility criteria

The inclusion and exclusion criteria for the trial are described in table 2.

**Table 2 T2:** Eligibility criteria

Inclusion criteria	Established diagnosis of PBC based on the presence of at least 2 out of the 3 key disease characteristics, specifically: Anti-mitochondrial antibody (AMA) or PBC-specific anti-nuclear antibodies (ANA) at a clinically diagnostic level. Elevated ALP (above the upper limit of normal (ULN) for the relevant laboratory). Compatible or diagnostic liver biopsy. Ongoing elevation of ALP (≥15% above ULN) at screening. Disease duration of <6 months from date of diagnosis at the time of consent. Use of UDCA for <3 months at the time of consent. Increased risk of not achieving disease remission with treatment (for the purposes of the trial defined as a pre-treatment ursodeoxycholic acid response score^10^ with a predicted risk of future non-remission of liver biochemistry (ie, ALP>ULN) with UDCA alone of >20%). For people of childbearing potential: an agreement to use at least an acceptable effective method of contraception or to practise sexual abstinence* to avoid pregnancy for the entire duration of the trial period. Willing to complete the trial assessment protocols. Ability to consent, able to comply with trial protocol and attend clinic visits. Age ≥18 years at the time of consent.

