Exclusion criteria	Clinical contraindication to obeticholic acid use. Untreated, clinically significant pruritus (patients with effectively treated pruritus are eligible for inclusion). Concomitant use of fibric acid derivatives (eg, bezafibrate or fenofibrate) within 14 days prior to screening. Clinical suspicion of cirrhosis evidenced by a history of one or more of the following: ascites requiring diuretic therapy or percutaneous drainage. endoscopically confirmed varices. liver biopsy suggesting cirrhosis. platelet count <150×10^9^/L. transient elastography score >16.9 kPa within 3 months prior to or at screening. hepatocellular carcinoma confirmed by biopsy or two imaging modalities. hepatic encephalopathy. Bilirubin >twice the ULN other than in the context of Gilbert’s syndrome or another cause of unconjugated hyper-bilirubinaemia. Evidence of complete biliary obstruction. Previous exposure to obeticholic acid (either in clinical trials or in clinical practice) or other potential PBC-modifying therapy. Regular (more than 1 week per month) alcohol consumption in excess of recommended safe limits (14 units per week). Active participation in another interventional trial or exposure to another experimental drug within five half-lives. Pregnancy or planning to get pregnant within the duration of participation in the trial. Currently breastfeeding. Overlapping features of an additional liver disease, including autoimmune hepatitis (using the Paris criteria for autoimmune hepatitis overlap). Hypersensitivity to the active substance or to any of the excipients. If the participant’s treating clinician deems the patient is not suitable to participate in the trial based on other criteria apparent during screening or from medical history. Previous liver transplantation.

* Abstinence is defined as refraining from heterosexual intercourse during the entire trial period. Abstinence is acceptable only as true abstinence: when this is in line with the preferred and usual lifestyle of the patient. Periodic abstinence (eg, calendar, ovulation, symptothermal, post-ovulation methods) and withdrawal are not acceptable methods of contraception.

ALP, alkaline phosphatase; PBC, primary biliary cholangitis; UDCA, ursodeoxycholic acid.

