Clinical review: Clinical history relevant to PBC and this trial, adapted according to the type of visit. At screening, this will include demographics, a detailed clinical review of PBC and its symptoms as well as medication history. At subsequent visits, this will include any changes in the history since screening, including any symptom changes or de novo symptom development and/or difficulties with taking medication.Clinical examination: A full physical examination will be conducted, including examination of skin; lymph nodes; eyes; ears; nose; throat; respiratory; cardiovascular; abdomen; musculoskeletal; neurological assessment; mental status assessment. Bodyweight will also be measured.Vital signs: Heart rate, blood pressure and temperature will be recorded.Blood sampling: A blood sample will be taken (maximum 50 mL) at times specified in figure 1 for the following assessments:Renal function: urea, creatinine and serum electrolytes.Liver biochemistry: alanine transaminase (ALT), aspartate aminotransferase (AST), alkaline phosphatase (ALP), total bilirubin, direct bilirubin, gamma-glutamyl transferase (GGT), albumin.Cholesterol (total cholesterol, Low Density Lipoprotein (LDL), High Density Lipoprotein (HDL), total:HDL ratio and triglycerides).Full blood count (haemoglobin, platelets and white cells—neutrophils and lymphocytes).Clotting: Prothrombin time and activated partial thromboplastin time.Experimental chemokine blood marker.Optional biobank blood sample.Clinical samples will be analysed in the clinical laboratories of the trial site, following standard local laboratory procedures.All chemokine samples will be analysed simultaneously at the end of the trial. All chemokine assessments will be performed in a fully blinded manner, with regard to treatment group and pre-therapy and post-therapy timing.There are three optional additional blood samples (baseline, visits 4 and 5) for use in future PBC research.Urine sampling: Participants will be asked if they are willing to provide consent to give two optional urine samples (baseline and visit 5).URS: Predicts the likelihood of someone responding to UDCA.^10^ URS must be calculated using the OPERA URS calculator that is provided as part of this clinical trial and available here: https://www.mat.uniroma2.it/~alenardi/URS.html.The URS calculator considers three different ‘cut-offs’ to define UDCA response. In this trial, we use the version that considers the outcome of interest to be biochemical remission (ie, ALP <1× upper limit of normal (ULN)). Based on the URS value, a predicted probability of biochemical remission can be calculated. For the purposes of trial eligibility, URS will be calculated using blood results prior to treatment with UDCA.Pregnancy testing: For people of childbearing potential, a pregnancy test will be carried out during the trial screening visit.EQ-5D-5L: A five-item, validated general quality of life measure from which health utility can be calculated.^26^PBC-40: A disease-specific, patient-derived multidomain quality of life measure. It has six domains relating to fatigue, cognitive symptoms, social function, emotional status and general symptoms.^5^Patient Health Questionnaire: A non-validated 5-point scale to assess health status perceived by participants in response to the trial medication at 26 and 52 weeks.Transient elastography (fibroscan): Clinically validated non-invasive tool used to assess liver stiffness; a surrogate marker of liver fibrosis.Compliance: Compliance regarding IMP will be checked at the interim telephone visit (4 weeks after taking IMP at day 0) and followed up at a clinic visit at week 12 and week 26. IMP compliance will be recorded in the Clinical Data Management System (CDMS). Pharmacy will count and record all returns received from each participant on the IMP accountability log. An accountability check will also be performed as part of on-site monitoring visits.

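### Secondary outcome (c) is already met at entry by participants enrolled with ALP 1.15 to <1.67×ULN and bilirubin <1×ULN, so it can count an unchanged state as response

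*Protocol article*

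**What the plan says.** Table 1 (Objectives and outcomes) defines secondary outcome (c) as the "Percentage of participants attaining serum alkaline phosphatase values lower than 1.67× the upper limit of normal" together with bilirubin below 1×ULN, both at week 26. The article calls these the POISE criteria. They are included to show the effect of OCA on the conventional response scale used in practice and in second-line trials. The definition sets two absolute levels. It requires no fall from baseline and leaves nobody out of the denominator.

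Table 2 (Eligibility criteria) sets the ALP floor as "Ongoing elevation of ALP (≥15% above ULN) at screening". On bilirubin it excludes "Bilirubin >twice the ULN", with an exception for Gilbert's syndrome and similar causes, so values between 1 and 2×ULN can enrol. It also permits "Use of UDCA for <3 months at the time of consent".

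The UDCA Response Score (URS) criterion concerns the predicted risk that ALP stays above 1×ULN on UDCA alone. Under Participant follow-up assessments, "URS will be calculated using blood results prior to treatment with UDCA".

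The Analysis section plans logistic regression for binary outcomes and, where they dichotomise a continuous variable, the augmented binary method. Baseline terms for that model are described for the primary outcome.

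**The concern.** The entry floor for ALP (1.15×ULN) lies below the response cut-off (1.67×ULN). A participant who enrols between the two with normal bilirubin has nothing left to attain. For example, someone entering at 1.3×ULN whose ALP climbs to 1.6×ULN, a 23% rise (1.6/1.3 = 1.23), is still a week-26 responder.

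Outcome (c) is there so that the result can be read against conventional response rates. If part of each arm meets the criterion at the start, the reported percentages mix response with entry status. The arm difference then depends partly on how many mild cases happened to enrol. A modest difference on (c) could be taken as a weak drug effect when it partly reflects the case mix.

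**Working it through.** **1. Thresholds side by side**

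| | ALP | Bilirubin |
|---|---|---|
| Allowed at entry (Table 2) | ≥1.15×ULN | ≤2×ULN |
| Counted under (c) at week 26 (Table 1) | <1.67×ULN | <1×ULN |
| Overlap | 1.15 to <1.67×ULN | <1×ULN |

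Both conditions must hold. A participant in the ALP band with bilirubin from 1 to 2×ULN does not meet (c) at entry.

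**2. Does another rule close the gap?** No. The URS criterion refers to 1×ULN, not 1.67×ULN. It uses pre-UDCA bloods, and up to 3 months of UDCA may precede consent, so screening ALP can be lower than the ALP behind the score. Randomisation is stratified only by biopsy consent.

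**3. The plan's own figure.** The article gives no assumed rates for (c). Its binary sample size for the primary outcome (20% v 45%, 5% two-sided, 90% power, Pearson χ²) can be reproduced, which checks the method used below:

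n per arm = [1.960·√(2×0.325×0.675) + 1.282·√(0.20×0.80 + 0.45×0.55)]² / 0.25² = 71.7, rounded up to 72. The total is 144, as stated.

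**4. Dilution.** Let f be the share meeting (c) at entry, s_T and s_C the probabilities that they still meet it at week 26 in the OCA and placebo arms, and p_T and p_C the response rates in the rest:

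difference = f·(s_T − s_C) + (1−f)·(p_T − p_C).

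If s_T = s_C, the first term is zero and the difference shrinks by (1−f).

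For illustration, take s = 1 in both arms and borrow the primary-outcome rates of 20% v 45% for the rest. With 48 per arm and a plain binary test:

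| f | Placebo | OCA | Difference | Power |
|---|---|---|---|---|
| 0 | 20.0% | 45.0% | 25.0 points | 75% |
| 0.2 | 36.0% | 56.0% | 20.0 points | 50% |
| 0.3 | 44.0% | 61.5% | 17.5 points | 40% |
| 0.5 | 60.0% | 72.5% | 12.5 points | 25% |

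At f = 0.3 the placebo figure is 0.30 + 0.70×0.20 = 0.44 and the OCA figure is 0.30 + 0.70×0.45 = 0.615. With 40% v 65% in the rest, power falls from 70% (f = 0) to 30% (f = 0.5).

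**5. How large might f be?** The article gives no baseline ALP or bilirubin distribution, so this is assumption only. For a log-normal ALP with median parameter m (×ULN) and log-SD σ, truncated at 1.15:

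P(ALP <1.67 | ALP ≥1.15) = [F(1.67) − F(1.15)] / [1 − F(1.15)].

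| m | σ = 0.4 | σ = 0.6 |
|---|---|---|
| 1.6 | 42.5% | 33.5% |
| 2.0 | 26.5% | 24.8% |
| 3.0 | 6.4% | 11.6% |

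For m = 3.0, σ = 0.4: (0.0715 − 0.0083)/(1 − 0.0083) = 0.064. For m = 1.6, σ = 0.4: (0.5426 − 0.2045)/(1 − 0.2045) = 0.425. The range is about 6–43% on ALP alone. The bilirubin condition can only lower it.

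**6. Does restricting the denominator cost power?** At f = 0.3 the restricted set has 48×0.7 = 33.6 per arm. At 20% v 45% the power is about 59%, against 40% for the diluted comparison. Under these assumptions the smaller denominator is not a net loss.

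**The case against.** The strongest reply is that nothing here is invalid. The trial is randomised and double-blind, entry responders are expected in both arms, and the percentage below a threshold at week 26 is a legitimate quantity to compare in the enrolled population. On that view, inflated and diluted make sense only relative to a different estimand, response among those not meeting the criterion at baseline. This stands as far as validity goes. A reader might infer that the definition favours OCA, and the documents do not support that.

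Secondary outcome (b) measures the ALP and bilirubin reductions from baseline as continuous variables, so a rise within the band would show there. The authors also say that conventional response indices tolerate ongoing disease activity, which is why normalisation is primary. Both points stand and limit the damage. The augmented binary analysis can use the continuous values and gain precision, but it does not alter what the percentage in (c) counts.

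The shrinkage by (1−f) assumes equal retention in both arms. If placebo participants drift out of the band and OCA participants do not, the entry group adds to the difference. With f = 0.3, s_T = 1 and s_C = 0.8, the difference is 0.3×0.2 + 0.7×0.25 = 0.235, that is 23.5 points rather than 17.5. The table in the working is therefore illustrative, not a forecast.

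Finally, a baseline breakdown or a subset analysis may sit in the full protocol or the SAP. Its absence from the article is not the point. The point is the definition that Table 1 does state.

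**Conclusion.** The point holds for one secondary outcome. As written, (c) is met before trial treatment by every participant enrolled with ALP 1.15 to <1.67×ULN and bilirubin <1×ULN, and it counts them as responders if they are unchanged or mildly worse. Response percentages rise in both arms and, with equal retention, the arm difference shrinks by (1−f).

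The threshold overlap is certain. Its size is not: f cannot be computed from the documents, and 6–43% is an ALP-only range under assumed distributions.

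Three stronger readings go too far:

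- That everyone in the ALP band is affected. Those with bilirubin of 1–2×ULN are not.
- That the state precedes all treatment. Up to 3 months of UDCA may come before consent, so it precedes trial treatment only.
- That the trial's main conclusion is at risk. Screening ALP of at least 1.15×ULN rules out biochemical remission at that time, so the primary outcome does not share the problem.

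A change to the definition is worth making, in proportion to a secondary outcome.

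**What to change.** Before unblinding, make one of two changes to (c) in the protocol and SAP.

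- **Add a prespecified minimum ALP fall from baseline.** A value of 15% would serve as an example. It is an assumed figure that the sponsor must justify. It would bind only below 1.67/0.85 = 1.96×ULN at baseline, because above that, reaching <1.67×ULN already implies a 15% fall. State which pre-treatment ALP value is the baseline.
- **Analyse (c) among participants not meeting it at baseline** (ALP ≥1.67×ULN or bilirubin ≥1×ULN). The subset is defined before trial treatment, so the randomised comparison is kept. Its size may differ between arms by chance, since ALP is not a stratification factor.

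Under either option, keep the all-participant version as supportive, so that the link to the conventional criterion is not lost. Report by arm the percentage already meeting (c) at baseline.

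The cost is outcome wording and SAP text, with no new data. The downside is lower response rates under the first option and a smaller denominator under the second.
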